## Abstract

**Background:**

Australian General Practitioners (GPs) are generous prescribers of antibiotics, prompting concerns including increasing antimicrobial resistance in the community. Recent data show that GPs in vocational training have prescribing patterns comparable with the high prescribing rate of their established GP supervisors. Evidence-based guidelines consistently advise that antibiotics are not indicated for uncomplicated upper respiratory tract infections (URTI) and are rarely indicated for acute bronchitis. A number of interventions have been trialled to promote rational antibiotic prescribing by established GPs (with variable effectiveness), but the impact of such interventions in a training setting is unclear. We hypothesise that intervening while early-career GPs are still developing their practice patterns and prescribing habits will result in better adherence to evidence-based guidelines as manifested by lower antibiotic prescribing rates for URTIs and acute bronchitis.

**Methods/design:**

The intervention consists of two online modules, a face-to-face workshop for GP trainees, a face-to-face workshop for their supervisors and encouragement for the trainee-supervisor dyad to include a case-based discussion of evidence-based antibiotic prescribing in their weekly one-on-one teaching meetings.

We will use a non-randomised, non-equivalent control group design to assess the impact on antibiotic prescribing for acute upper respiratory infections and acute bronchitis by GP trainees in vocational training.

**Discussion:**

Early-career GPs who are still developing their clinical practice and prescribing habits are an underutilized target-group for interventions to curb the growth of antimicrobial resistance in the community. Interventions that are embedded into existing training programs or are linked to continuing professional development have potential to increase the impact of existing interventions at limited additional cost.

**Trial registration:**

Australian New Zealand Clinical Trials Registry, ACTRN12614001209684 (registered 17/11/2014).

**Electronic supplementary material:**

The online version of this article (doi:10.1186/s12875-016-0470-7) contains supplementary material, which is available to authorized users.

## Background

Antimicrobial resistance is a serious and increasing threat to global public health and it is linked to the over-prescription of antibiotics [1, 2]. The majority of antibiotics consumed by humans are prescribed in primary care [2, 3], and they are often prescribed in conditions for which there is no evidence of benefit [4, 5]. For example, initial use of antibiotics is not of benefit in acute upper respiratory tract infections (URTIs) and is associated with an increase in adverse effects [6]. For acute bronchitis, antibiotics are associated with limited benefits of doubtful clinical significance [4].

Evidence-based therapeutic guidelines are widely used in general practice. The *“Australian Therapeutic Guidelines: Antibiotic v15”* for example recommend symptomatic (non-antibiotic) treatment for acute uncomplicated URTIs and advise that acute bronchitis is most often viral and usually does not require antibiotic therapy [7]. Availability and knowledge of guidelines, however, does not guarantee adherence which is reflected in the level of over-prescribing of antibiotics [8]. Data from Australian general practitioners (GPs) in training showed that antibiotics are prescribed in 22 % of presentations for URTIs, and 73 % of bronchitis/bronchiolitis [9]. These prescription rates are comparable to those of established GPs. This clear overprescribing of antibiotics suggests that more effort needs to be directed towards changing the prescribing habits of clinicians.

In high-income countries, public campaigns at a regional and national level using a variety of multimedia platforms, have been directed at the public, child-care staff and health professionals [10]. Most campaigns also encouraged the use of guidelines in the components that targeted prescribers. Results from some multifaceted campaigns repeated over several years suggest a positive effect on antibiotic use, but others seem to have had little if any effect [10]. The means by which the prescribing patterns of GPs might be influenced is still the focus of debate. In primary care, a variety of interventions aimed at influencing individual doctors’ prescribing have been studied, including audit and feedback [11], small group meetings [12], and academic detailing [13]. Systematic reviews have established that in primary care and ambulatory practice, multi-faceted interventions that include combinations of the above approaches [14] and active, rather than passive, interventions [15] are the most successful in reducing antibiotic prescribing for inappropriate indications.

Unfortunately, the size of the effect of these approaches has been limited. For instance, a UK randomised control trial incorporated the above principles in an intervention to reduce antibiotic prescribing by GPs [16]. This produced a modest decrease in antibiotic prescribing of 4.2 % in the intervention relative to the control practices. Moreover, the intervention was expensive and cost £2923 per practice – several times the estimated annual savings in antibiotics cost. The European GRACE consortium, however, showed an encouraging and likely more affordable way to achieve meaningful reductions in antibiotic prescribing for lower respiratory tract infections [17]. This intervention used online training modules on communication skills and on the use of C-reactive protein (CRP) to distinguish bacterial from presumed viral infections. Both communication training and introduction of CRP separately resulted in a reduction of antibiotic prescribing, with the combination achieving the largest effect (communication intervention risk ratio: 0 · 68; CRP: 0 · 53; combined intervention: 0 · 38) [18].

It is plausible that interventions targeted at an early, receptive stage of GPs’ careers might be more efficacious. Early-career GPs may be a singularly appropriate target for intervention. They are at a stage of their clinical careers where their prescribing patterns are unlikely to be firmly established and are thus more amenable to modification. Unlike hospital-based junior doctors, early-career GPs are working in the clinical environment where they will spend the rest of their careers, so education regarding long-term prescribing practices will be contextually relevant. Because experienced clinicians have already established consulting and antibiotic prescribing habits that have been shown to be resistant to change [19], we hypothesise that focused educational interventions that target GPs in training whom are still developing their own practice “style” and prescribing “habits”, could be more effective in improving adherence to evidence-based guidelines.

## Methods/design

The ChAP study (Changing the Antibiotic Prescribing of general practice registrars) aims to improve the antibiotic prescribing of early-career GPs. In this study we propose to develop an Australian educational intervention based on components of the INternet TRaining for antibiOtic use (INTRO) intervention, developed in Europe [17]. To assess the effectiveness of the intervention, ongoing quantitative data collection from the Registrar Clinical Encounters in Training (ReCEnT) Study will be utilized [20]. We will evaluate the intervention’s impact on antibiotic prescribing of early-career GPs for two classifications of respiratory tract infections (URTI and acute bronchitis/bronchiolitis).

### Study design

We will use a non-randomised non-equivalent control group design. Data for the analyses will be collected during the six-monthly rounds of ReCEnT data collection. The ReCEnT study is an ongoing prospective multi-site cohort study of GP registrars/trainees' consultations in five of Australia’s 17 Australian GP regional training providers [20]. ReCEnT longitudinally documents the nature and association of consultation-based clinical and educational experiences of early-career GPs (GP trainees). GP trainees record details of 60 consecutive consultations at approximately the mid-point of three six-month (full-time equivalent) terms based in general practices. Details recorded include patient demographics, diagnoses/problems managed, medications prescribed, investigations ordered, and assistance sought during the consultation (including supervisor advice and use of guidelines).

### Outcome measures

#### Primary outcomes

The primary outcomes will beChange in proportion of consultations (from pre-intervention to post-intervention ReCEnT data collection periods) for URTIs in which antibiotics are prescribedChange in proportion of consultations (from pre-intervention to post-intervention ReCEnT data collection periods) for bronchitis/bronchiolitis in which antibiotics are prescribed.

#### Secondary outcomes

Secondary outcomes will beChange in proportion of consultations (from pre-intervention to post-intervention ReCEnT data collection periods) for bronchitis/bronchiolitis and URTI (combined) in which antibiotics are prescribed.Change in proportion of consultations (from pre-intervention to post-intervention ReCEnT data collection periods) for sore throat in which antibiotics are prescribedChange in proportion of consultations (from pre-intervention to post-intervention ReCEnT data collection periods) for acute sinusitis in which antibiotics are prescribedChange in proportion of consultations (from pre-intervention to post-intervention ReCEnT data collection periods) for acute otitis media in which antibiotics are prescribed

Respiratory tract infections will be defined by International Classification of Primary Care, 2nd Edition (ICPC-2) disease diagnostic codes R74 (URTI) and R78 (bronchitis/bronchiolitis) [21].

We will define acute sore throat as the ICPC-2 codes R72 (strep throat), R76 (tonsillitis, acute), R74008 (pharyngitis, acute), R74006 (infection, throat), R74017 (pharyngitis) and R21005 (sore throat). Codes R72001 (scarlet fever), R72003 (scarlatina) and R72004 (scarlet fever) will be excluded from the analysis, as antibiotics are recommended for all cases of these conditions in the authoritative Australian guidelines [22].

We will define acute sinusitis as those presentations coded as R75 (excluding R75003 and R75004 as these are codes for chronic and allergic sinusitis respectively).

Acute otitis media will be defined as those presentations coded as H71 (excluding H71008, H710018 and H710019 as these are codes for ear inflammation, abscess and mastoiditis).

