### Data collection and analysis

Change in antibiotic prescribing will be assessed via ReCEnT data pre- and post-intervention. The changes in GP trainees’ prescribing will be compared with the changes of GP trainees of the two regional training providers who are not receiving the intervention (control group).

The principal analysis will be logistic regression within a Generalised Estimating Equation framework to adjust for clustering of observations within GP trainees. The unit of analysis will be consultations involving a respiratory tract infection and the outcome factor will be antibiotics prescribed (dichotomous). Independent variables in the model will be treatment group (intervention/control), time (before/after) and an interaction term of treatment group by time. The p-value of the interaction term will be used to determine statistical significance.

The dependent variables in regression models will be consultations in which antibiotics are prescribed (for URTI and acute bronchitis/bronchiolitis separately as the primary outcomes, and for URTI plus acute bronchitis/bronchiolitis (combined), acute otitis media, acute sinusitis and sore throat as the secondary outcomes).

We will also consider trainee, patient, practice and consultation related factors in the regression analyses. GP trainee factors will be age, gender, training term, place of medical qualification (Australia/international), and full-time/part-time status. Patient factors will be age, gender, Indigenous (Aboriginal or Torres Strait Islander) status, Non-English-speaking background status, whether new patient to the practice, and whether a new patient to the GP trainee. Practice factors will be rurality/urbanicity, socioeconomic status of the practice location, and practice size (number of GPs). Practice postcode will be used to assign the Australian Standard Geographical Classification-Remoteness Area (ASGC-RA) classification (the degree of rurality) of the practice location [30] and to define the practice location’s Socioeconomic Index for Area (SEIFA) Relative Index of Disadvantage [31]. Consultation factors will include the number of diagnoses/problems dealt with during the consultation, if the problem was a new one, and if the GP trainee sought clinical assistance during the consultation (from their supervisor/trainer, from a specialist, or from electronic or hard-copy resources).

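### Two of the three exclusion codes for acute otitis media appear mistyped and, if applied as printed to six-character codes, would exclude nothing

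*Protocol article*

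**What the plan says.** The Secondary outcomes section of the Protocol article fixes each respiratory outcome at the level of ICPC-2 codes. Acute otitis media is rubric H71, with three extended codes taken out: "excluding H71008, H710018 and H710019 as these are codes for ear inflammation, abscess and mastoiditis".

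The same section defines the other outcomes in the same way:

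- Sore throat takes in rubrics R72 and R76 and four extended codes, "R74008 (pharyngitis, acute), R74006 (infection, throat), R74017 (pharyngitis) and R21005 (sore throat").
- It then drops three more: "Codes R72001 (scarlet fever), R72003 (scarlatina) and R72004 (scarlet fever) will be excluded from the analysis".
- Acute sinusitis is R75, "excluding R75003 and R75004 as these are codes for chronic and allergic sinusitis respectively".
- URTI and bronchitis/bronchiolitis are the whole rubrics R74 and R78.

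The Data collection and analysis section gives each condition its own regression model and lists "acute otitis media, acute sinusitis and sore throat as the secondary outcomes", next to the combined URTI and bronchitis outcome.

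**The concern.** An outcome defined by a code list is only as good as the codes. In this section an extended code is a three-character rubric followed by a three-digit term number. Two of the otitis media exclusions break that pattern: they carry four digits after H71.

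The codes form part of an operative definition that decides which consultations enter a model. A filter given a code that does not exist in the data produces no warning; it simply removes no records. The plan names the conditions it wants out of the outcome. If the codes fail, consultations for some of those conditions are counted, contrary to the definition, and nobody need notice. A reader who tried to reproduce the outcome from the printed codes would meet the same problem.

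**Working it through.** The plan gives no figure to reproduce here. The check is a comparison of code formats, followed by a matching exercise.

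**Step 1: formats.** The Secondary outcomes section contains 18 distinct codes.

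| Format | Codes | Count |
|---|---|---|
| Letter + 2 digits (3 characters) | R72, R74, R75, R76, R78, H71 | 6 |
| Letter + 5 digits (6 characters) | R74006, R74008, R74017, R21005, R72001, R72003, R72004, R75003, R75004, H71008 | 10 |
| Letter + 6 digits (7 characters) | H710018, H710019 | 2 |

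The total is 6 + 10 + 2 = 18. No code outside the otitis media sentence has seven characters.

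**Step 2: internal evidence of a slip.** H71008 stands in the same list, under the same rubric, with a three-digit term. A two-digit term number also appears elsewhere, in "R74017 (pharyngitis"): term 17 is written 017, with one leading zero. H710018 and H710019 write 18 and 19 with two leading zeros. This is what an extra zero typed in both codes would look like.

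**Step 3: what the printed codes would do.** Take every possible code of the form H71 plus three digits, H71000 to H71999, which is 1,000 codes. Compare each printed exclusion with them.

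| Printed code | Exact matches | Codes beginning with it | Cut to six characters |
|---|---|---|---|
| H71008 | 1 | 1 | H71008 |
| H710018 | 0 | 0 | H71001 |
| H710019 | 0 | 0 | H71001 |

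On data in the six-character format, the second and third exclusions remove nothing. A program that cut the strings to six characters would turn both into H71001. That is a different string from either printed code, and the plan does not list it for exclusion.

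**Step 4: which conditions would remain.** Three codes and three conditions are listed. Read in order, H71008 is ear inflammation, H710018 abscess and H710019 mastoiditis. The sinusitis sentence states that its codes and conditions correspond in order; the otitis media sentence does not. The pairing is the natural reading but is inferred. Whatever the pairing, two of the three exclusions are affected.

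**Step 5: reach.** Only the acute otitis media outcome uses H71. The two primary outcomes and the combined outcome rest on R74 and R78, and the sore throat and sinusitis codes are regular in format.

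**The case against.** The best defence is that this is a typing slip in a condensed journal article. The excluded conditions are named in words, so anyone holding the code list can recover what was meant, and nothing shows that the analysis program carries the same error. The article shows neither the ReCEnT code table, nor the stored code format, nor how the filter is implemented. All of this stands, and it makes the consequence conditional. It does not remove the point: the definition as printed cannot be applied with confidence, and the document itself shows that the two codes are irregular.

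A reader might go further and infer that the exclusions will certainly fail and that the otitis media effect will be pulled towards zero in proportion to the share of abscess and mastoiditis consultations. The document does not support that, for four reasons.

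- Failure requires both six-character records and literal use of the printed strings. Neither is established.
- No count or share of these conditions is given, so any percentage would be a guess.
- Dilution by exactly that share would hold for a difference in proportions if prescribing in these records did not change and their share were equal in both groups and both periods. The planned test is a group-by-time interaction in a logistic GEE model, where the change in the log-odds effect need not equal the share.
- The article does not say that the H71 exclusions are there to isolate discretionary prescribing. It gives a treatment reason only for the scarlet fever codes; for H71 it says only what the codes stand for.

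**Conclusion.** The two codes appear mistyped, and the definition needs correcting or verifying. The format evidence is complete within the document: ten of the twelve extended codes have six characters, and the two that do not sit in one sentence.

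The consequence rests on two assumptions, that ReCEnT stores these terms in the six-character format and that the printed strings are used unchanged. If both hold, two of the three otitis media exclusions do nothing, by list order those for abscess and mastoiditis. The size and direction of any effect on the result cannot be determined from the document. The matter is minor: it concerns one secondary outcome, the same definition applies to both groups and both periods, and the primary outcomes are not affected.

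**What to change.** Look up both codes in the ICPC-2 term list used in ReCEnT and replace them with the valid codes for the conditions named in the sentence. The format alone would suggest H71018 and H71019, but that is a guess to be checked and should not be adopted without the list. State in the definition which code belongs to which condition, as the sinusitis sentence does. Before the analysis is run, tabulate the H71 records by extended code before and after the filter and confirm that those for the named conditions have gone.

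The cost is one look-up, a one-line correction and one tabulation. Nothing in the design, data collection or model changes.

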### Setting

The intervention will be delivered once to GP trainees in two Regional Training Providers (RTPs). GP trainees in three control training providers will receive usual educational activities. These are five of the 17 RTPs in the Australian general practice vocational training program. The demographics of the GP trainees in the intervention group are broadly comparable to those of the control training providers.

### The intervention

The intervention in the ChAP study consists of four components. The first three i.e. access to an online introduction module, an online communication training module, and an interactive workshop, are delivered separately to GP trainees and to supervisors. The fourth is an optional joint GP trainee-supervisor activity, which comprises a case-based discussion of evidence-based antibiotic prescribing for each trainee-supervisor dyad in their regular weekly one-on-one teaching meetings. An overview of the study design and content of the intervention is provided in Fig. 1.

**Fig. 1 Fig1:**
[figure not shown]
Study design. ChAP study, Changing the Antibiotic Prescribing of general practice registrars; ReCEnT study, Registrar Clinical Encounters in Training; URTIs, Upper Respiratory Tract Infections (upper respiratory tract infections and bronchitis/bronchiolitis); INTRO, INternet TRaining for antibiOtic use

#### INTRO modules

The first two components (online introduction and communication training modules) are based on the INTRO intervention. INTRO is part of a European multi-country study (GRACE consortium) aimed at reducing inappropriate antibiotic prescribing for lower respiratory tract infections in primary care [17]. One of the main advantages of INTRO is that it is a brief and cost-effective intervention. The introduction module discusses the need for reduced antibiotic prescribing and the effect of over-prescription on the health care system, patients and GPs. It covers the epidemiology of URTIs in primary care, Australian and international antibiotic use and antimicrobial resistance, and the evidence-base of current clinical guidelines. The communication training module consists of videos showing how a GP can use communication skills to elicit patient concerns and expectations, discuss the pros and cons of antibiotic treatment and the natural course of respiratory tract infections, whilst maintaining patient satisfaction. The communication training module is supported by a patient booklet. These two modules were adapted for the Australian context with particular reference to the Australian Therapeutic Guidelines: Antibiotic. Version 15 (version 2013): TG [7].

The online modules will be made available to GP trainees to work through individually at a time that best suits them. They will be given a timeframe in which to complete the modules. A face-to-face workshop will be scheduled after completion of the electronic modules in order to maximise the potential for effectiveness.

The INTRO modules will also be made available to the trainee’s supervisors in the two intervention RTPs, again prior to scheduled separate supervisor workshops (see below).

#### Workshops

The workshop component consists of a 1.5 h interactive workshop, scheduled as part of the standard training program for GP trainees and delivered at the premises of their RTP. We will use data on GP trainees' prescribing collected in the ReCEnT project to contextualise and reinforce the practical relevance and importance of the educational message (the ReCEnT data will be that of the workshop attendee trainees and their more senior colleagues who have been collecting ReCEnT data since 2010) [20]. During the workshop sessions, GP trainees will be asked to reflect on their group’s prescribing data and by means of clinical cases work through the main principles of rational prescribing of antibiotics informed by the authorative Australian guideline on antibiotic use (eTG). During the workshop there will be room for practising the communication skills presented in the online modules.

There will be ‘content’ discussion in the workshops, which will expand upon and explore some of the issues covered in the online modules. This discussion will present URTIs and acute bronchitis as exemplars of respiratory tract infections for which antibiotics are rarely indicated. Discussion will focus on these clinical syndromes, but the tenets of rational prescribing will also be applied to other non-pneumonia respiratory tract infections for which antibiotics have very limited indications (sore throat, acute otitis media, acute sinusitis).

Three underlying principles will inform the approach presented in the discussion: Firstly, that the default position for non-pneumonia respiratory tract infections is to *not* prescribe antibiotics. Deviation from this principle in any particular case requires careful consideration of the rationale for prescribing in that individual patient’s circumstance. Secondly, treatment of non-pneumonia respiratory tract infections should be on syndromic rather than aetiological basis. Delineation of viral versus bacterial aetiology is difficult and non-contributory and does not reflect current understanding of the complex interplay of bacterial and viral pathogens [23, 24]. A syndromic approach to management reflects the empirical evidence for treatment in the area [5, 25–27]. Thirdly, that the clinical science of consultations for non-pneumonia respiratory tract infections may be straightforward but managing patient expectations may be complex and require advanced communication skills, i.e. the sophistication of consultation techniques employed should reflect the biopsychosocial complexity of the consultation rather than the biological complexity of the clinical presentation.

The workshop content will be constructed by the research team of GPs, GP vocational training educators, academic GPs and an infectious diseases physician/researcher. The process will be informed by the current literature in the area and our recent work in early-career GPs' antibiotic prescribing – the prevalence and associations of antibiotic prescribing for URTI and acute bronchitis/bronchiolitis and the qualitative experiences of GP trainees in managing URTI and acute bronchitis [9, 28].

The same workshop will be delivered separately to the supervisors in the two intervention RTPs.

